#### Service integration

Service integration will be measured mid-way through 2021 with respect to a 2019 baseline, and then annually for the duration of the project, using two validated tools. First, the Human Services Integration Measure (HSIM) by Browne et al. [18] will be given to all relevant organisations within the Belconnen district and all services and programs within the nine intervention suburbs. The tool (Appendix 3 in S1 File) is designed to gauge how each service perceives their current level of collaboration with other related services. To better reflect the context of the integration, the rating scale in the tool will be slightly adapted. Adaptations include a slight rewording of the rating explanations to better reflect the nature of service integration for early childhood centres and services and the addition of questions asking services to list the names of other services they have been involved with that did not appear on the survey. The tool will be distributed and completed using Qualtrics^XM^ (Qualtrics Australia, Sydney) online survey software. This will ensure the form is easy to complete and that all completed forms are returned and filed for data analysis.

The second tool, Successful Collaborations by Winkworth and White [19] will be administered to services that have indicated collaborations with other services on the HSIM tool. The Successful Collaborations tool (Appendix 4 in S1 File) aims to quantify the depth and scope of a collaboration between two services across three domains: capacity, authority, and shared value. The tool will be distributed, completed, and the data analysed online.

Representatives will also be invited to participate in a recorded interview. This interview will explore the collaboration in more depth and attempt to understand how service providers understand and use the term ‘integration’ and how they perceive the value and benefit of integrating services.

#### Within intervention measures

Within the allied health programs embedded into early childhood services and the publicly available programs, such as community playgroups and loose parts play sessions, measures of reach, dose, fidelity, environment, and outcomes will be gathered.

For the *Learning Language and Loving It* speech pathology program, several measures will be collected. The Teacher Interaction and Language Rating Scale (TILRS) [20] will be used to measure the effects of the intervention on the instructional practices and skills of the early childhood educators before and after participating in the program. Other child measures including phonological and print knowledge tests and receptive/expressive one-word picture vocabulary tests will be employed by the clinical educator and speech pathology students to gauge the effects of the intervention on children’s linguistic productivity and emergent literacy skills.

Measures for occupational therapy programs and support will include detailed field notes and program specific outcomes. The measures for the *Parents as Teachers* [21] child development program include process indicators such as the number of educators trained, and the number of sessions completed (taking in retention and staff churn). Facilitators will also collect data on the number of children from each intervention suburb that will be reached by the program.

Tools to assess the ECEC environment will also be used. The Early Language and Literacy Classroom Observation (ELLCO) [22] tool will be used to assess how well each centre supports and encourages positive literacy practices. The checklist includes questions on the book area, book selection, book use, writing materials, and writing around the room [23]. The Early Childhood Environment Rating Scale (ECERS-E) [22] will be used to evaluate the quality of the classroom environment. The questionnaire covers space and furnishings, personal care, language and literacy, learning activities, interaction, and program structure [24]. This measure will be used to assess the ECEC’s ability to implement the skills and practices they have learnt during the intervention and to foster and encourage early literacy and language skills.

Two measures will be collected from the student-led Kids at Play program (based on the Kids at Play Active Play program). A pre- and post-program survey will be administered to participants to gauge educator confidence to teach fundamental movement skills and promote active play and educators’ perceptions of the benefits of play. This survey was created by ACT Health but will have amendments from the Good Start In Life team. An Active Play Audit tool [25] will also be completed with the centre educators and/or director. This tool assesses the centre environment and aids educators in creating an active play policy and a Quality Improvement Plan for the centre, which will be re-evaluated 6 months post-intervention.

The community playgroups and loose parts play sessions will have sign-in sheets that will capture demographic information on the children attending. This includes age, cultural background, and gender of each child, and which suburb each family lives in (Appendix 5 in S1 File). No identifying information will be collected from any participant. Suburb information will be collected to assess the proportion of children attending from the intervention suburbs.

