## Introduction

Early childhood experiences and interactions have a profound influence on a child’s physical, cognitive, social and emotional development [1, 2] and form the critical foundation for their lives [3–5]. The social circumstances into which children are born determines their exposure to events that are either beneficial or detrimental to their development [6]. How well children grow and thrive depends on the nurturing conditions of their environment in the widest sense, and this is fundamentally important in the early years (under 5 years) when the brain and body are developing rapidly [7]. The primary provider of beneficial early development opportunities are the child’s parents and caregivers. However, most parents cannot provide strong supportive environments without the assistance of formal and informal support services When parental support is compromised, for example due to factors such as sustained poverty, family break-up, family violence, abuse, neglect, illness or disability, then some of the child’s beneficial development opportunities must be provided by external support mechanisms. Unfortunately, contemporary trends indicate that the prevalence of such adverse circumstances in Australia have been worsening [8].

In response to this issue, the Australian government established the Australian Early Development Census (AEDC) in 2009, to provide a national measurement programme to monitor Australian children’s development. The AEDC is undertaken every three years. There have been four waves of measurement, the last one being completed in 2018. The census involves teachers of children in their first year of full-time school (age 5–6 years) completing the Australian version of the Early Development Instrument [9]. The Instrument consists of approximately 100 behavioural and competency-based questions and collects data relating to five key areas of early childhood development, referred to as ‘domains’. These include: physical health and well-being; social competence; emotional maturity; language and cognitive skills (school based); communication skills and general knowledge.

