To achieve the second aim of this project, allied health programs will be embedded and delivered ‘in place’ into early childhood services within the intervention suburbs. Through a partnership with the University of Canberra, students from speech pathology, occupational therapy, health, nutrition, and education disciplines will work with a clinical educator to implement programs into early childhood services as a part of their work integrated learning. The programs will either function as professional learning for ECEC educators and playgroup facilitators or provide on-site clinical advice and support.

To supplement the aims and objectives of this project, other existing services and activities will be delivered to target suburbs within the community. Formal partnerships, marked by the creation of memoranda of understanding between organisations and the project, will be developed to ensure a clear understanding of the aims and scope of the partnership as well as to facilitate the creation or modification of services and programs to better address the needs of children and their families. This may include creating new programs, providing resources or funding to facilitate existing programs within intervention suburbs, or expanding current programs to reach more children and families. Within intervention suburbs, ‘loose parts play’ and ‘nature play’ as enabling environments will be held in suitable local settings e.g. parks, community halls, public spaces [16]. These place-based activities will be open to the public in non-stigmatising ways to engage local parents and caregivers who may not have been previously involved with other services due to lack of accessibility.

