### Data collection

Measures relating to both the overarching project aims and individual interventions will be collected pre- and post-intervention. Measures of service integration will be collected annually throughout the project for both control and intervention sites.

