## Discussion

In this paper, we present the design of a quasi-experimental study in which we conduct a process and outcomes evaluation of a multi-sector, multi-component programme of interventions for improving the physical and mental health of children who are at the highest risk of developmental vulnerability and disadvantage in the ACT. The focus of providing a family liaison coordinator in important behaviour settings within the child’s environment, i.e., early childhood education, playgroups and community settings, is considered a strength of this intervention.

The interventions will be implemented in collaboration with local professionals and community members. Community co-design during conceptualisation, development and planned implementation is central to this study. Participatory approaches ensure end-users and service provider voices are heard and provide an understanding of local practice and context to ensure more authentic engagement with community members in the target areas.

In addition to the outcome evaluation, a process evaluation will be conducted to provide insights into the implementation of the interventions and the role of the local context. The link between effectiveness and implementation are important for developing and scaling future health promotion interventions.

To monitor intervention effectiveness multiple data collection tools are used to measure the different outcomes. Firstly, fidelity measures are collected to ensure the programs and interventions are implemented as intended. Incorrectly or incompletely implemented programs may result in the intervention having no effect on educator professional knowledge and practice, and therefore these measures must be collected to account for any lack of significant differences in the primary outcome measure. These outcomes will be detailed in the process evaluation. Other data collected, including the AEDC results, service integration survey scores, and data from the speech pathology and occupational therapy programs, will be used to form the outcome evaluation. This evaluation is used to assess the extent to which the project delivered the outcomes outlined in the planning program logic and if there were any significant improvements in developmental vulnerability in children in the Belconnen district that may have been influenced by this project.

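### The clinical educator and students who implement the language programme also give the child tests that judge it, which tilts those programme-level results toward benefit by an unknown amount

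*Protocol article*

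**What the plan says.** All references are to the Protocol article.

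- **Delivery** (Design and intervention): "students from speech pathology, occupational therapy, health, nutrition, and education disciplines will work with a clinical educator to implement programs into early childhood services". The same section describes the form that delivery takes: "The programs will either function as professional learning for ECEC educators and playgroup facilitators or provide on-site clinical advice and support".
- **Testing** (Within intervention measures): for the speech pathology programme, the child tests "will be employed by the clinical educator and speech pathology students to gauge the effects of the intervention".
- **Timing** (Data collection): "Measures relating to both the overarching project aims and individual interventions will be collected pre- and post-intervention".
- **Use** (Discussion): "data from the speech pathology and occupational therapy programs, will be used to form the outcome evaluation".

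The article names no separate, masked or external tester for the child tests. It specifies independent work by two researchers only for coding the qualitative material (Qualitative analyses). The limitations in the Discussion cover suburb-level data, concurrent projects and activity in the control area, but not the overlap between testers and deliverers.

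**The concern.** Testing young children individually leaves the tester some discretion over how far to prompt, whether to accept a borderline answer and when to stop. A tester who belongs to the delivering team, knows whether the session is before or after the programme, and would like it to work may use that discretion more generously at the second test. The error then runs in the same direction as the hoped-for effect, and no later analysis can separate the two.

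What is at stake is the claim that this programme improves children's language and emergent literacy. These tests are the only direct child language measures that the article names for it, and they enter the outcome evaluation as evidence of effect, not only as process monitoring.

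**Working it through.** The article gives no sample size, standard deviation or target difference for these tests, so no arithmetic applies. The check is a comparison of the relevant statements.

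1. **Do the roles coincide?** Design and intervention puts delivery in the hands of students, speech pathology among their disciplines, working with a clinical educator. Within intervention measures puts the child testing in the hands of the clinical educator and speech pathology students. The two roles are the same. The article has named its testers, so this is a stated choice and not a gap left to a fuller document.

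2. **Is the overlap shown for individuals?** No. Nothing says that the student who worked in a given centre tests the children there, or that one student tests the same child twice. Nothing separates them either. The finding is an overlap of roles.

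3. **Do the testers know the time point?** Within intervention measures ties its timing phrase to the educator rating scale, which covers "instructional practices and skills of the early childhood educators before and after participating in the program". It does not repeat that timing for the child tests. The pre/post schedule for those tests therefore rests on the general statement under Data collection, which covers individual interventions. If that statement applies, programme staff would know which session is which.

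4. **Do the results count as outcome evidence?** Yes. The tests are given to gauge the intervention's effects, and the Discussion includes speech pathology programme data in the outcome evaluation.

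5. **How far does the problem reach?** The Introduction says of the census: "The census involves teachers of children in their first year of full-time school"; those teachers complete the instrument. The hypotheses under Quantitative analysis concern six census indices, one primary and five secondary. The child language tests are not among them. The problem is confined to programme-level results.

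6. **Size.** The article offers nothing from which to derive it. Any figure would only restate whatever shift and standard deviation were assumed, so none is given.

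**The case against.** The case on the other side has five parts.

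- **Contact with children may be slight.** If the programme works mainly by training educators, students and the clinical educator may hardly know the tested children. This stands. A reader might infer that children will be more at ease with the tester at the second test and score higher for that reason. The article does not support this, because it does not say how much direct contact there is. Knowledge of the programme and a stake in the result remain without it.
- **Who tests in which centre is operational detail.** This is partly right: a reader might infer that each student tests the children he or she served, and the article does not say so. But it does assign the testing to the delivering roles, so the starting position is overlap unless a rule prevents it.
- **Structured naming and vocabulary tests leave less room for expectation than rating scales.** This is fair. It bears on the size of the bias, not on its presence.
- **No comparison group is described for these tests, so a gain could not be attributed to the programme anyway.** This is true, and changing the testers does not cure it. It is a separate weakness. It strengthens the case for cautious reporting and does not excuse a second source of error in the same direction.
- **The study's main conclusions do not depend on these tests.** This is correct. A reader might infer that the primary result is compromised; it is not, because these staff do not complete the census instrument.

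**Conclusion.** The concern holds in a limited form. The article gives delivery of the language programme and testing of its effect on children to the same roles, and it uses the results as outcome evidence. The expected direction of bias is toward the programme, and its size is unknown. The conclusion assumes that the general pre/post rule covers the child tests and that no rule outside the article keeps testers away from centres they served. It does not depend on rapport with the children or on the same person testing twice. The primary outcome and the five secondary indices are untouched, so this is a worthwhile correction to a programme-level measure and not a threat to the main analysis.

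**What to change.** **Change under Within intervention measures.** State that students will be rostered so that, as far as numbers allow, no student tests children in a centre where he or she delivered the programme, at either time point. State also that the clinical educator supervises testing but does not test in centres he or she served. The article refers to a single clinical educator; if that person supports every centre, he or she would supervise only.

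**Where separation is not possible.** Report the results as descriptive pre-post change, add the overlap between testers and deliverers to the limitations in the Discussion, and do not present the gain as a programme effect.

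**Optional.** Score recorded responses in random order by someone not told the time point, but only where consent covers recording. The article mentions recording for interviews and describes no consent to record children's tests, so consent might need extending. A further scorer might also be needed.

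**Cost.** Rostering work and some travel between centres. The roster draws on existing students, but the article gives no student numbers, so how complete the separation can be is unknown. Testers would still be programme staff who know the time point. The bias is reduced and not removed, and the absence of a comparison group for these tests remains.

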### Data analysis

#### Qualitative analyses

Interviews will be audio taped, transcribed verbatim and imported into NVIVO qualitative data analysis software. We will be following the procedure outlined by Braun et al. (2019) for using thematic analysis to analyse qualitative data [26]. Interview transcripts and observation narratives will be coded thematically by two researchers independently. Details will be collected on the contents of the interventions, service experiences of collaboration and the family liaison coordinator role.

#### Quantitative analysis

Testing for statistically significant differences in children’s early development indices will be based on the critical difference approach developed for the AEDC by Gregory and Brinkman [17]. The Gregory and Brinkman report provides the technical details to determine “how big” a difference (%) needs to be in the EDI results between two different time points or two different areas to be considered statistically significant [11, Tables 14 –primary outcome and 13 –the five secondary outcomes, respectively]. The method allows for the expected sample to sample variation and typical measurement error associated with the sort of data collected in the AEDC. Current versions of the methodology allow us to compare two point-estimates, either across time or between neighbourhoods, of the selected index. Table 1 shows the critical differences that will be needed to establish a significant change for each of the six EDI indices,—the primary outcome and five secondary outcomes—to be considered in this study. The population of children in the intervention and control areas is expected to be in the range 200–299 at the 2024 census. Time-point comparisons will be made between 2021 and 2024 AEDC indices for both intervention and comparator areas. Across-area comparisons will be made between intervention and comparator areas for the 2024 census indices. The following hypotheses will be tested for each of the six indices to be used in this study:

Each EDI for the intervention suburbs (within the Belconnen district) for the 2024 census will be significantly lower, i.e. show a significant reduction in the proportion of children who are developmentally vulnerable or at risk, compared to that in the control suburbs (within the Tuggeranong district)Each EDI for the intervention suburbs (within the Belconnen district) for the 2024 census will be significantly lower, i.e. show a significant reduction in the proportion of children who are developmentally vulnerable or at risk, compared to the corresponding value in the 2021 census

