Over the last three censuses (2012–2018), the Australian Capital Territory (ACT) has seen an increase in the proportion of children who are developmentally vulnerable on all but one of the AEDC domains and the two summary domains, vulnerable on one or more domains and vulnerable on two or more domains [10]. As a result, early childhood development has been a focus recently in the ACT. Early investigations have shown that services, organisations, and sectors continue to operate in isolation, and, as a result, it has been reported that families struggle to access cohesive and holistic pathways of care for their children. Examining the variation in early childhood vulnerability across suburbs making up the ACT’s nine districts reveals greater developmental vulnerability is experienced in clusters of suburbs. According to the 2018 AEDC, 26.4% of 5-year-old children in the Belconnen district were developmentally vulnerable in one or more domains [11].

An inventory of all early childhood services in the Belconnen district in 2019 revealed that there were multiple services across the education, health, and social services sectors in operation. These included but were not limited to Early Childhood Education and Care (ECEC) services, playgroups, preschools and parenting programs. However, evidence suggests that vulnerable families are unable to or choose not to access these services, or are not aware of them [12]. The fragmented nature of service delivery and accessibility, particularly across centres and services, hinders referrals and restricts pathways of care for children with developmental needs. Under these conditions developmental issues are not addressed, while the number of children entering school with significant social, communication, behaviour and health challenges continues to increase. Research confirmed that when such challenges are present on entering formal education, there are cascading effects throughout the school years and later in life [3, 4]. These children are more likely to experience poor academic achievement, early drop-out from school and unemployment [13].

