*Sample size estimates*. Our sample size calculation is based on the AEDC ‘critical difference estimates for communities’ [17]. We will focus the intervention on those suburbs (SA2) in the two poorest performing districts with the highest proportions of children with at least one EDI domain in the developmentally vulnerable category at the most recent census. For example, based on 2018 census results, ~40% of this sample have been classified as developmentally ‘at risk’, i.e. falling significantly behind their peers, and could benefit from early intervention. We anticipate that approximately half of this number, ~250–300 children, will be required to show a statistically significant difference. Our primary focus will be on reducing the number of children who are developmentally vulnerable on at least one index (Table 1). We will also perform separate tests for change in the percentage of children at risk in each of the five EDIs.

**Table 1 pone.0267666.t001:** Critical differences (%) to establish significant change for each of the six early development indices.

Community size (# of children)	Developmentally vulnerable (1+) (%)	Physical Health & wellbeing (%)	Social competence (%)	Emotional maturity (%)	Language & cognitive skills (%)	Communication & general knowledge (%)
200–299	4.7	5	4.6	4.9	4.8	5.2

Time-point comparisons will be made between 2021 and 2024 AEDC indices for both intervention and comparator areas. Across-area comparisons will be made between intervention and comparator areas for the 2024 census indices.

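### The 4.7-point critical difference for the primary outcome is too small, at a conventional 5% level, to cover sample-to-sample variation with 200–299 children per area

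*Protocol article*

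**What the plan says.** The Quantitative analysis section of the protocol article bases significance testing on a critical-difference method taken from a cited AEDC technical report. It describes the method's scope in these words: "Current versions of the methodology allow us to compare two point-estimates, either across time or between neighbourhoods, of the selected index". It then states what the method covers: "The method allows for the expected sample to sample variation and typical measurement error associated with the sort of data collected in the AEDC".

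Table 1, in the sample-size paragraph under Developmental vulnerability, is captioned "Critical differences (%) to establish significant change for each of the six early development indices". It has one row: "200–299 4.7 5 4.6 4.9 4.8 5.2". The first figure after the size band, 4.7, is for the primary outcome (vulnerable on one or more domains). The other five are for the single domains.

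That row is chosen because of the expected numbers: "The population of children in the intervention and control areas is expected to be in the range 200–299 at the 2024 census". The same thresholds serve two directional hypotheses: the intervention suburbs lower than the control suburbs in 2024, and the intervention suburbs lower in 2024 than in 2021. The section gives no alpha, confidence level or sidedness.

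Two prevalence figures are available. The Introduction gives a district rate: "26.4% of 5-year-old children in the Belconnen district were developmentally vulnerable in one or more domains". The sample-size paragraph says "based on 2018 census results, ~40% of this sample have been classified as developmentally" at risk, for the targeted suburbs.

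**The concern.** The rule compares two estimated proportions, each from a few hundred children. Both vary by chance, and at a prevalence near one quarter the standard error of their difference is close to 4 percentage points. A threshold of 4.7 points is then little more than one standard error. Such a threshold cannot cover sample-to-sample variation at a conventional 5% level, let alone measurement error on top of it.

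This is the decision rule for the primary outcome, and the same approach is applied to the five domains. If the threshold is too low, ordinary differences between cohorts or areas can be reported as a significant reduction in vulnerability when the programme has had no effect.

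**Working it through.** **Inputs**
- Threshold: 4.7 points (Table 1).
- Children: 200–299, read as per area (Quantitative analysis). Evaluated at n = 200, 250 and 299.
- Prevalence: p = 26.4% (Introduction). The figure of about 40% (sample-size paragraph) is used as a higher value, although the text attaches it to children at risk.
- Alpha and sidedness: not stated. A 5% level is assumed and both sidednesses are shown.
- Model: two independent binomial groups of equal size, with no measurement error and no clustering.

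**Attempt to reproduce 4.7**

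SE of the difference = √(2p(1−p)/n). At p = 0.264, 2 × 0.264 × 0.736 = 0.3886.

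| n per area | SE (points) | two-sided 5%: 1.96 × SE | one-sided 5%: 1.645 × SE |
|---|---|---|---|
| 200 | 4.41 | 8.6 | 7.3 |
| 250 | 3.94 | 7.7 | 6.5 |
| 299 | 3.61 | 7.1 | 5.9 |

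No two-sample rule at 5%, one- or two-sided, gives 4.7. The near matches are a two-sample 80% interval at n = 299 (4.62 points, but 5.65 at n = 200) and a one-sample 90% interval at n = 250 (4.59 points), which ignores variation in the second estimate.

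**False-positive rate at 4.7 points when there is no true difference**

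z = 4.7/SE; one-sided rate = 1 − Φ(z); two-sided rate = 2(1 − Φ(z)).

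| p | n | z | favourable direction | two-sided |
|---|---|---|---|---|
| 26.4% | 200 | 1.07 | 14.3% | 28.6% |
| 26.4% | 250 | 1.19 | 11.7% | 23.3% |
| 26.4% | 299 | 1.30 | 9.6% | 19.2% |
| 40% | 200 | 0.96 | 16.9% | 33.7% |
| 40% | 250 | 1.07 | 14.2% | 28.3% |
| 40% | 299 | 1.17 | 12.0% | 24.1% |

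Exact binomial sums at 26.4% agree: 14.1%, 12.2% and 8.9% in the favourable direction. As an illustration of clustering, an assumed design effect of 1.5 raises the two-sided 23.3% at n = 250 to 33.0%.

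**Size at which 4.7 would be a 5% threshold**

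n = 2p(1−p)(z/0.047)². At 26.4% this is about 676 per area two-sided (z = 1.96) and 476 one-sided (z = 1.645). At 40% it is about 835 and 588.

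**The other sample size in the document**

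The sample-size paragraph takes about 40% of the sample and calls half of that number 250–300 children. Then 40% of the sample is 500–600, and the sample is 500/0.40 = 1,250 to 600/0.40 = 1,500. With that many per area, the two-sided rate at 4.7 points and 26.4% is 0.8% to 0.35%. If it is the total over two equal areas (625–750 each), the rate is 5.9% to 3.9%. Either way 4.7 would be roughly adequate or better, but neither size agrees with the 200–299 used to choose the Table 1 row.

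**The case against.** **Alpha and sidedness are the reader's assumption.** This stands. Both hypotheses are directional, so only the favourable tail yields a false claim of benefit. A reader might take 19–34% as the plan's actual error rate, but that rests on a two-sided level the document never states. The favourable-direction rate is 10–17%. This does not rescue the threshold, because one-sided 5% at 26.4% still needs 5.9–7.3 points.

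**The derivation is in a report not at hand.** This stands too. A reader might conclude that the AEDC method is itself faulty. The documents do not support that: its confidence level and variance model are not shown. What can be shown is that 4.7 does not fit the coverage claimed for it here, at this size and prevalence and at a conventional level.

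**A census has no sampling error.** That is so for describing one year's children in one place. This plan compares different cohorts and different areas to ask whether a programme reduced vulnerability, and it claims the coverage itself.

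**The group sizes may be larger.** The Design section names the whole Tuggeranong district as control. If the control figure were in effect free of chance variation, the favourable-direction rate at 4.7 would be 6.6%, 4.6% and 3.3% at n = 200, 250 and 299. But the Quantitative analysis section speaks of control suburbs and expects 200–299 in both areas. The 2021-to-2024 comparison within the intervention suburbs would also not benefit.

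**The order of the Table 1 values.** A reader might infer further proof from the fact that four of the five domain thresholds exceed 4.7, although vulnerability on any domain is at least as common as on a single one. That inference is sound only if the domain indices count vulnerable children. The text also describes them as at risk, or as vulnerable or at risk, and measurement error may differ by index. The finding does not rely on it.

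**Conclusion.** The point holds in limited form. As written, the primary decision threshold is inconsistent with the coverage the plan claims for it. Assuming 5%, independent groups of 200–299 per area and 26.4% prevalence, the threshold falls short by about 1.2–2.6 points one-sided (5.9–7.3 against 4.7) or 2.4–3.9 points two-sided (7.1–8.6 against 4.7). The chance of a false favourable finding is about two to three times a one-sided 5% for each comparison. These figures are lower bounds under that model, since measurement error and clustering are left out. If the true group sizes are nearer the 1,250–1,500 implied by the sample-size paragraph, 4.7 would be adequate, but the wrong row of the source table would then have been used. One of the two statements has to change.

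**What to change.** 1. State the alpha and sidedness for the primary and secondary comparisons.
2. Reconcile the sample-size paragraph (about 1,250–1,500 children by its own arithmetic) with the 200–299 in the Quantitative analysis section, and say whether the control is the whole district or selected suburbs.
3. Base the significance decision on the estimated difference in proportions with a 95% CI, computed from the suburb-level AEDC results and numbers of children. The variance should be at least binomial. With only nine intervention suburbs, make an allowance for suburb-level overdispersion or clustering a sensitivity analysis, not the main result.
4. Keep the Table 1 critical difference as a descriptive supplement, and remove the statement that it covers sample-to-sample variation at this size.

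The cost is a less favourable threshold and a little more analysis. No new collection should be needed, provided that numbers assessed are available with the suburb-level percentages. The Discussion says that data are released at suburb level but does not say whether counts are included, so this should be confirmed.
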